#### Secondary outcomes

The secondary outcomes are:Total HAMD score at 4 weeks after childbirthMajor depressive disorder (MDD) as determined by the depression module of the Mini International Neuropsychiatric Interview (MINI) [39] at 12 weeks after starting the intervention and at 4 weeks after childbirth-MINI is a concise structural interview for the major Axis I psychiatric disorders described in the Diagnostic and Statistical Manual of Mental Disorders, Fourth Edition and the International Classification of Diseases and Related Health Problems, Tenth RevisionTotal scores on the EPDS [40] at 12 weeks after starting the intervention and at 4 weeks after childbirth-EPDS is a widely used 10-item self-report scale to assess the severity of perinatal depressive symptoms in the past week; EPDS scores > 9 may indicate the presence of MDD [41]Beck Depression Inventory II (BDI-II) [42] at 12 weeks after starting the intervention and at 4 weeks after childbirth-BDI-II is a widely used 21-item self-report scale to measure the severity of depressive symptoms in the past 2 weeks [42]; it was not designed to perinatal mood specifically but has been used during pregnancy and in the postpartum period [28, 43]Biomarkers levels at baseline, 12 weeks’ follow-up, and 1 month after childbirth forOmega-3 fatty acids concentrations in erythrocytesBrain-derived neurotrophic factor (BDNF) in serumEstrogen in plasmaOxytocin in plasmaProgesterone in plasmaHuman chorionic gonadotropin in plasmaPhospholipase A2 in plasma

For the measurement of biomarkers, plasma and serum will be drawn at baseline, at 12 weeks’ follow-up, and at 1 month after childbirth. Samples will be stored in separate freezers at−80 °C until analysis. All samples will be analyzed on the same day and under the same conditions by a biochemist blinded to the severity of depressive symptoms and participants’ diagnostic status.

### Other outcomes

Standard obstetric outcomes will be analyzed: gestational age, gestational diabetes mellitus, gestational hypertension or preeclampsia, induced labor, estimated blood loss, cesarean section, operative vaginal delivery, birthweight, 1-min and 5-min Apgar scores, and neonatal intensive care unit admission. Data will be collected on discontinuation of the allocated interventions.

### Participant protection and reporting of adverse events

We define an adverse event as any unwanted or unintended sign, symptom, or disease observed in the trial participants, whether or not it is caused by study intervention. Safety issues will be monitored by interview, telephone, or email. Researchers and clinical research coordinators will record and evaluate any suspected adverse events. The follow criteria will guide evaluation of the severity of adverse [34].Mild: Some symptoms or signs observed. Treatment is not required for the participant to continue in the trial.Moderate: Some symptoms or signs observed. The participant may reduce the dose of test capsules or receive treatment such as additional drugs to continue the trial.Severe: Clinical symptoms are severe enough to interfere with daily activities. Discontinuation of test capsules may be necessary.

The following are always regarded as serious adverse events, regardless of test dosage.An event that results in deathA life-threatening eventAn event that requires hospitalization (or extends an existing hospitalization period) in order to provide treatmentAn event that results in a permanent or prominent disorder or a failure in body functionAn event that results in a subsequent congenital anomaly or deficiencyOther events considered medically significant

Any serious adverse event will be reported to and assessed by the Data and Safety Monitoring Board as soon as possible. The ethics committee will also receive the report. Other adverse events will be reported and evaluated regularly. Information on concomitant drug use and reason for use will also be reported.

### Estimation of sample size

The expected difference in total HAMD score between the two arms at 12 weeks’ follow-up is set at 4.7 according to a previous study [28]. It is expected that 12 % of participants will discontinue the test capsules or drop out of the trial. Given an α level of 0.05 (two-tailed), a β level of 0.10, and standard deviation of 5, the desired number of participants will be 28 in each arm and 56 in total. Because a previous study suggested that seafood consumption varied across countries [33] and this may have a major effect on the efficacy of omega-3 PUFAs, 56 participants will be recruited at each site in Japan and Taiwan. Thus, the total number of participants will be 112. However, it is possible that enrollment will be halted before reaching this target if significant financial or logistical factors arise, or that number of cases at one of the sites may exceed the target number depending on the accumulation of cases at the other site.

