**Methods:**

The Synchronized Trial on Expectant Mothers with Depressive Symptoms by Omega-3 PUFAs (SYNCHRO) is a multicenter, double-blind, parallel group, randomized controlled trial. Participants will be randomized to either the omega-3 PUFAs arm (1,200 mg eicosapentaenoic acid and 600 mg docosahexaenoic acid daily) or placebo arm. Primary outcome is total score on the Hamilton Rating Scale for Depression (HAMD) at 12 weeks after the start of the intervention. We will randomize 56 participants to have 90 % power to detect a 4.7-point difference in mean HAMD scores with omega-3 PUFAs compared with placebo. Because seafood consumption varies across countries and this may have a major effect on the efficacy of omega-3 PUFA supplementation, 56 participants will be recruited at each site in Taiwan and Japan, for a total number of 112 participants. Secondary outcomes include depressive symptoms at 1 month after childbirth, diagnosis of major depressive disorder, changes in omega-3 PUFAs concentrations and levels of biomarkers at baseline and at 12 weeks’ follow-up, and standard obstetric outcomes. Data analyses will be by intention to treat. The trial was started in June 2014 and is scheduled to end in February 2018.

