## Methods/Design

SYNCHRO is a multicenter, double-blind, parallel group, randomized controlled trial that will allocate participants to an intervention arm to receive omega-3 fatty acid supplementation or a parallel placebo arm in the ratio of 1:1. The trial will run from June 2014 through February 2018, with participant enrollment between June 2014 and August 2017.

The study was registered at clinicaltrials.gov (NCT02166424) on June 15, 2014 and the University Hospital Medical Information Network (UMIN) Center (UMIN000017979) on June 22, 2015.

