### Statistical analysis

#### Primary analysis

Primary analysis will be conducted according to the intention-to-treat principle. Mean score differences, 95 % confidence intervals, and P values will be calculated using analysis of covariance in order to examine whether participants receiving omega-3 PUFAs supplementation score on average 4.7 points lower on the HAMD at 12 weeks’ follow-up than participants receiving placebo. Two-tailed tests will be used, with the α level set at 5 %. The assignment remains masked, but any background factors that may predict primary outcome will be entered as covariates if such factors are found.

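### The 90 % power belongs to one country's 56 women, not to the pooled primary comparison of 112, and the per-country number behind 112 is neither used in the primary analysis nor protected

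*Protocol article*

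**What the plan says.** All references are to the protocol article.

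- **Estimation of sample size.** The inputs are: "The expected difference in total HAMD score between the two arms at 12 weeks’ follow-up is set at 4.7"; "Given an α level of 0.05 (two-tailed), a β level of 0.10, and standard deviation of 5"; "It is expected that 12 % of participants will discontinue the test capsules or drop out of the trial". They give 28 per arm, 56 in all. Because seafood intake differs between countries and could alter efficacy, the number is then doubled: "56 participants will be recruited at each site in Japan and Taiwan. Thus, the total number of participants will be 112".
- **Abstract, Methods.** The 90 % is attached to 56 women, as "power to detect a 4.7-point difference in mean HAMD scores with omega-3 PUFAs compared with placebo". The same reason is given for taking 56 in each country.
- **Estimation of sample size, last sentence.** Enrolment may stop short of the target for financial or logistical reasons, or the "number of cases at one of the sites may exceed the target number depending on the accumulation of cases at the other site".
- **Primary analysis.** Intention-to-treat ANCOVA compares women on omega-3 with women on placebo for HAMD at 12 weeks. "Two-tailed tests will be used, with the α level set at" 5 %. No country-specific test, country term or division of alpha is mentioned. Covariates are background factors found to predict the outcome.
- **Exploratory analysis.** Secondary outcomes and subgroups are exploratory, without multiplicity control. Country is not named.
- **Randomization.** Current MDD and study site are the stratification factors.

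**The concern.** The only reason given for 112 rather than 56 is that efficacy may differ between Japan and Taiwan. That is an argument for enough women in each country to learn something there. The primary analysis does not use the sample in that way, and the exploratory section does not mention country. The recruitment clause then allows the per-country number to slip. The power statement, the reason for 112 and the primary analysis therefore do not describe the same test.

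Three things are at stake:

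- Readers of the abstract will take 90 % for 4.7 points as the power of the trial's main comparison, which it is not.
- If the feared heterogeneity is real, the pooled test has much less power than 90 %, and nothing in the article says so.
- With no country analysis specified, a result that looks different in the two countries could be described after the event by setting two P values side by side, which is not a test of a difference.

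**Working it through.** **Inputs (protocol article).** Difference 4.7, SD 5, two-sided alpha 0.05, power 0.90 and loss 12 % come from Estimation of sample size. Allocation is "a parallel placebo arm in the ratio of 1:1" (Methods/Design). Any precision gained from ANCOVA covariates is ignored throughout, because no correlation is given.

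**Step 1. The plan's own figure.** Normal approximation, per arm:

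n = 2 × SD² × (1.96 + 1.28)² / difference² = 2 × 25 × 10.51 / 22.09 = 23.8, rounded up to 24.

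Allowing for loss: 24 / 0.88 = 27.3, rounded up to 28 per arm, or 56 in total. This matches exactly.

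**Step 2. One country at 56.** Evaluable per arm: 28 × 0.88 = 24.64. Standard error of the difference: 5 × √(2/24.64) = 1.42. Power for 4.7 by the noncentral t: 89.8 % (90.3 % if rounded to 25 per arm). The stated 90 % holds for this test.

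**Step 3. The pooled comparison of 112.** Evaluable per arm: 56 × 0.88 = 49.28. Standard error: 5 × √(2/49.28) = 1.007.

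| Scenario | Pooled effect | Power |
|---|---|---|
| Same effect, 4.7, in both countries | 4.7 | 99.6 % |
| Same effect, 3.3, in both countries | 3.3 | 90 % |
| 4.7 in one country, 0 in the other, equal sizes | (4.7 + 0)/2 = 2.35 | about 64 % |

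The 12 % covers women who stop capsules as well as those who drop out, and the article says women who stop are still followed. Treating all 12 % as lost is therefore the cautious end. With no loss (56 per arm) the three results become 99.9 % for 4.7, 90 % for about 3.1 points, and about 69 % for 2.35.

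**Step 4. If recruitment shifts.** The article gives no figures for a shift, so these country totals are assumptions. Evaluable per arm = total × 0.88 / 2.

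| Women in the smaller country | Evaluable per arm | Power for 4.7 |
|---|---|---|
| 56 | 24.64 | 90 % |
| 50 | 22.0 | 86 % |
| 40 | 17.6 | 77 % |
| 28 | 12.32 | 61 % |

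**Step 5. The comparison between countries.** The contrast of the two country effects has standard error 5 × √(4/24.64) = 2.01. For a true difference of the full 4.7 points, 4.7 / 2.01 = 2.33, and power is about 64 %. Even at the full 56 per country, the trial is weak on the question that led to 112.

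**The case against.** The strongest reply is that the arithmetic is right and the design is benign. The 90 % is tied explicitly to 56 women and reproduces. Primary analysis and Exploratory analysis, read together, point to one pooled test at 5 %, with any country analysis exploratory. On that reading type I error is intact, and if the effect is common the trial has more power than promised. The recruitment clause openly discloses possible imbalance, names no split, and lets the larger country gain power. Model terms and subgroup details may be in an analysis plan that is not shown.

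Much of this stands, and it rules out some stronger readings that a reader might infer:

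- *That the power figure is wrong however the analysis is read.* It is not: at 56 per country it is correct for each country.
- *That the trial cannot say which test decides success.* The natural reading is the pooled test, although the article never says in so many words that it is pooled.
- *That there are two co-primary country tests with an inflated false-positive rate.* The text provides for no such tests.
- *That the recruitment clause abolishes per-country power.* It permits erosion; it does not plan it. At 50 women the power is still about 86 %.

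What does not fall is the mismatch within the article's own statements. It gives a power figure and a per-country reason for 112, then a primary comparison to which neither applies. An analysis plan could settle the pooling, but the article would still state no power for the analysis of 112. The common-effect assumption behind the reassuring 99.6 % is the one that Estimation of sample size calls into question.

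**Conclusion.** The concern holds in this form, at moderate severity. The 90 % for 4.7 points describes one country that reaches 56 women. It is not the power of the pooled primary test, which is about 99.6 % for a common 4.7-point effect, with 90 % power for about 3.3 points, but about 64 % if the effect is 4.7 in one country and absent in the other. The per-country power that motivated 112 is not used in the primary analysis and not protected in recruitment: about 77 % at 40 women and 61 % at 28.

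These figures rest on SD 5, 12 % loss taken as missing data, equal arms, no covariate gain and, for the shortfalls, assumed country totals. "Pooled" is the natural reading of the primary analysis, not an explicit statement in it. Validity of the primary test is not threatened; what suffers is the match between the stated power, the reason for the sample size and the analysis.

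**What to change.** 1. **Primary analysis.** State that the primary test is the pooled ANCOVA of all randomised women at two-sided 5 %, adjusted for the stratification factors, site and current MDD.
2. **Abstract and Estimation of sample size.** Say that 90 % for 4.7 points applies to a single country that reaches 56. Add the figure for 112: 90 % for about 3.3 points, or over 99 % for 4.7, assuming the same effect in both countries, with about 64 % if it is 4.7 in one and 0 in the other.
3. **Country results.** Prespecify country-specific differences with 95 % confidence intervals and the treatment-by-country contrast as secondary estimates. Note the contrast's low power (SE about 2.0; about 64 % for a 4.7-point difference), and state that no country difference will be inferred from separate P values.
4. **Substitution sentence.** Add that per-country power falls below 90 % if a country ends below 56, with an example.

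The cost is wording in the protocol and analysis plan. No extra women are needed, and because the trial was still enrolling with assignment masked, the changes can be made before unblinding. The one price is that country-specific claims are plainly secondary.

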### Statistical analysis

#### Primary analysis

Primary analysis will be conducted according to the intention-to-treat principle. Mean score differences, 95 % confidence intervals, and P values will be calculated using analysis of covariance in order to examine whether participants receiving omega-3 PUFAs supplementation score on average 4.7 points lower on the HAMD at 12 weeks’ follow-up than participants receiving placebo. Two-tailed tests will be used, with the α level set at 5 %. The assignment remains masked, but any background factors that may predict primary outcome will be entered as covariates if such factors are found.

#### Exploratory analysis

We will conduct exploratory analysis of secondary outcomes and sub-groups and therefore multiplicity will not be controlled. A mixed effect model with repeated measures will be evaluated by regression. The validity of the findings will be examined through sensitivity analysis, including per protocol analysis and analysis of the method used to impute missing variables.

### Ethical considerations

This study protects the rights and welfare of participants in the spirit of ethical guidelines outlined under the Declaration of Helsinki. Informed consent to participate in the study will be obtained from all participants. Personal information about potential and enrolled participants will be strictly secured to avoid external leaks before, during, and after the trial. No special compensation will be paid in the event of health damage directly related to the research. The research plan was deliberated on and approved by the following ethics committees: Tokyo Medical University, Japan, 26 June 2013; and China Medical University, Taiwan, 6 December 2013. If the protocol needs to be changed for any reason, the principal investigators will communicate this with the institutional review boards.

### Data and safety monitoring

The data manager will use a premade template to create a report to be sent to the principal investigator and the Data and Safety Monitoring Board once every 6–12 months. The members of the Data and Safety Monitoring Board are [name] (psychopharmacology), [name] (clinical psychiatrist), and [name] (psychotherapy), who are professionals with clinical trial experience with no involvement in the trial. The monitoring report includes the following.Progress of the study and case registrationPsychiatric evaluation status and any relevant issuesAny adverse eventsDiscussion of other relevant issues

### Discontinuing intervention

Intervention will be discontinued if the participant does not wish to continue taking the trial substance or placebo, or if continuing the intervention would be difficult because medically required concomitant medication may be affected by the trial substance. Subsequent evaluations and follow-up will proceed as designed.

### Presentation of the trial results

The findings of the trial will be presented in medical journals and at academic conferences. If particularly noteworthy results are obtain or the study is accepted by an influential academic publication, an application for a press release will be made. The principal investigators are, in general, listed as corresponding authors. The order of presentation of the first author and co-authors will be determined according to their intellectual contributions. Individuals who join the study after its approval and work toward implementing and conducting the study may obtain authorship pending approval by the principal investigators.

## Discussion

The findings of the SYNCHRO study are expected to influence decisions on the clinical care of pregnant women with depressive symptoms. The strengths of the study include its double-blind, placebo-controlled design, its multicenter, multi-country collaboration, and its evaluation of an EPA-rich supplement.

Maternal depression can have a significant harmful influence on both mothers and children. Due to the possibility of adverse effects of antidepressants, omega-3 PUFAs may provide a safe alternative for pregnant women with depressive symptoms. So far, only 2 RCTs have examined the efficacy of omega-3 PUFAs with a high ratio of EPA for depression in pregnancy [28, 43]; one of which recruited pregnant women without current depression but with a history of depression [43]. In addition, the result of one study on omega-3 PUFAs conducted in one country may not be able to be applicable to other countries due to differences in fish consumption [33]. The SYNCHRO study should provide evidence for two different populations in Asia and contribute to promoting mental health of large numbers of mothers and children.

## Trial status

This randomized trial is now enrolling participants and conducting follow-up.

## Abbreviations

BDI-II: Beck depression inventory II
BDNF: Brain-derived neurotrophic factor
CBT: Cognitive behavioral therapy
DHA: Docosahexaenoic acid
EPA: Eicosapentaenoic acid
EPDS: Edinburgh postnatal depression scale
HAMD: Hamilton rating scale for depression
IPT: Interpersonal psychotherapy
MDD: Major depressive disorders
MINI: Mini international neuropsychiatric interview
PUFA: Omega-3 polyunsaturated fatty acid
RCT: Randomized controlled trial
